## Abstract

**Background:**

In patients submitted to major pulmonary resection, the postoperative length of stay is mainly influenced by the duration of air leaks and chest tube removal. The measurement of air leaks largely relies on traditional chest drainage systems which are prone to subjective interpretation. Difficulty in differentiating between active air leaks and bubbles due to a pleural space effect may also lead to tentative drain clamping and prolonged time for chest drain removal. New digital systems allow continuous monitoring of air leaks, identifying subtle leakage that may be not visible during daily patient evaluation. Moreover, an objective assessment of air leaks may lead to a reduced interobserver variability and to an optimized timing for chest tube removal.

**Methods:**

This study is a prospective randomized, interventional, multicenter trial designed to compare an electronic chest drainage system (Drentech™ Palm Evo) with a traditional system (Drentech™ Compact) in a cohort of patients undergoing pulmonary lobectomy through a standard three-port video-assisted thoracic surgery approach for both benign and malignant disease. The study will enroll 382 patients in three Italian centers. The duration of chest drainage and the length of hospital stay will be evaluated in the two groups. Moreover, the study will evaluate whether the use of a digital chest system compared with a traditional system reduces the interobserver variability. Finally, it will evaluate whether the digital drain system may help in distinguishing an active air leak from a pleural space effect, by the digital assessment of intrapleural differential pressure, and in identifying potential predictors of prolonged air leaks.

**Discussion:**

To date, few studies have been performed to evaluate the clinical impact of digital drainage systems. The proposed prospective randomized trial will provide new knowledge to this research area by investigating and comparing the difference between digital and traditional chest drain systems. In particular, the objectives of this project are to evaluate the feasibility and usefulness of digital chest drainages and to provide new tools to identify patients at higher risk of developing prolonged air leaks.

**Trial registration:**

ClinicalTrials.gov, NCT03536130. Retrospectively registered on 24 May 2018.

## Background

Length of stay (LOS) impacts significantly on health-care costs. In patients submitted to major pulmonary resection, the LOS is mainly influenced by the duration of air leaks and chest tube removal, which are the main factors that delay hospital discharge. Prolonged air leaks affect between 10 and 15% of pulmonary surgical procedures and may be a risk factor for increased morbidity, prolonged hospital stay and increased costs [1, 2]. The measurement or grading of air leaks still relies on a static analog measurement of “bubbles in a chamber” using traditional chest drainage systems. These systems are inherently prone to subjective interpretation and observer variability conditioned by habit and personal clinical experience [3]. Moreover, the difficulty in differentiating between an active air leak and bubbles due to a pleural space effect, which are indistinguishable on checking a traditional water-seal chest drain system, may lead to tentative drain clamping and prolonged time for chest drain removal.

The introduction of novel digital chest drainage systems could give specific advantages.

First of all, they could give an objective assessment of real air leak, reduce interobserver variability and, finally, optimize the timing of chest tube removal. Continuous monitoring of air leaks may identify subtle leakage that may not be visible during daily patient evaluation. Moreover, these systems could distinguish an active air leak from an apparent air leak due to a pleural space effect through the evaluation of differential intrapleural pressures [4]. Finally, these systems could identify patients at higher risk of prolonged air leak and this could be useful in prompting either early active intervention or conversion to a one-way valve system that would allow for outpatient management and therefore early discharge from the hospital [5]. Some of these systems feature portable suction systems, allowing earlier mobilization of the patients, thus reducing complications due to bed immobility. To date, few studies (mostly single-center studies with small numbers of patients) have been performed with the aim to evaluate the clinical impact of digital drainage systems [5, 6]. The works published on this subject were performed using different electronic devices: some of them use an air flow meter to directly measure the airflow through the chest tube, whereas others derive these data from an algorithm based on the intrapleural pressure maintained by a suction pump and measured through a pressure sensor [5, 7, 8].

These previous studies proved that electronic drainage systems contribute to early mobilization, shorten the duration of chest tube placement, and thus hospital stay, and reduce costs using a more accurate and objective air leak assessment. Moreover, these systems are more effective in standardizing postoperative management of chest tubes [6, 7]. These advantages have particular importance in patients undergoing pulmonary resection with an underlying pulmonary disease such as COPD [9]. Finally, another possible advantage is to avoid tentative clamping since digital drainage eliminates subjective estimation. Brunelli et al. [5] described the possibility of predicting the risk of prolonged air leak after pulmonary lobectomy through the analysis of both air leak flow and pleural pressure. Such analysis cannot obviously be performed through a standard water-seal chest drain system.

All of these studies underlined the potential clinical utility and impact of electronic drainage systems; however, prospective randomized studies with a large number of patients are needed to corroborate these results.

Therefore, we intend to perform a trial to compare electronic chest drainage system performances to those of a traditional system in a prospective cohort of patients who received thoracoscopic lobectomy. Both systems are currently used in our daily clinical practice.

### Primary outcomes

To determine whether the use of a digital chest system compared with a traditional system reduces the duration of chest drainage and LOS

#### Primary outcome measures

To determine whether the use of a digital chest system compared with a traditional system reduces the duration of chest drainage and LOS, and to evaluate the role of interobserver variability, the duration of chest tube stay, the hospital length of stay and the daily presence of active air leaks will be evaluated in the two groups.

### Secondary outcomes

To quantify the variability of results regarding the subjective observer evaluation of active air leaks (through the traditional system) compared with the objective data registered by the digital systemTo distinguish an active air leak from a pleural space effect by the evaluation of intrapleural differential pressureTo identify potential predictors of prolonged air leaks

#### Secondary outcome measures

To distinguish an active air leak from a pleural space effect and to identify potential predictors of prolonged air leaks, the digital chest system will record and evaluate the intrapleural differential pressure, the flow of air leaks and the daily variation of these two parameters in each patient.

## Methods/design

This study is designed as a prospective randomized, multicenter, investigator-initiated study, of an interventional type, performed at three high-volume Italian thoracic surgery units: Thoracic Surgery Unit of Padua University Hospital, Thoracic Surgery Unit of Fondazione IRCCS Cà Granda Ospedale Maggiore Policlinico— University of Milan and Thoracic Surgery Unit of Vito Fazzi Hospital, Lecce.

This protocol is reported in line with the Standard Protocol Items: Recommendations for Interventional Trials (SPIRIT) guidelines using the SPIRIT figure (Fig. 1), trial flow chart (Fig. 2) and SPIRIT Checklist (Additional file 1).

**Fig. 1 Fig1:**
[figure not shown]
Standard Protocol Items: Recommendations for Interventional Trials (SPIRIT) figure for the schedule of enrollment, interventions and assessments. CT computed tomography, ECG electrocardiogram, PET positron emission tomography

**Fig. 2 Fig2:**
[figure not shown]
Trial flow chart. los length of stay

The study will enroll 382 patients undergoing pulmonary lobectomy through a standard uniportal, biportal or triportal VATS approach, either for benign or malignant disease.

The sample size was calculated considering a two-sided *t* test for a difference in means outcome, according to the following assumptions: effect size = 0.33 for both primary endpoints, power (1 – β) = 0.8 and α = 0.025 accounting for a Bonferroni adjustment (α = 0.05 / 2) [10]. The sample size computation was performed with R software [11].

Potential participants will be identified and recruited into the trial by surgeons who work in the aforementioned thoracic surgery units.

Patients will be enrolled if they meet the inclusion criteria specified afterward and sign the informed consent form (ICF).

An interim analysis will be performed on the primary endpoint when 200 patients are enrolled and randomized.

### Inclusion criteria

Able and willing to read, understand and provide written informed consentPatients undergoing VATS lobectomyAge 18–80 yearsGender: bothEstimated life expectancy of at least 6 months.Tumor considered potentially resectable by R0 surgeryAdequate respiratory function for surgery, particularly a predicted postoperative (ppo) forced expiratory volume in 1 s (FEV1) greater than 30% and a ppo carbon monoxide lung diffusion capacity (DLCO) greater than 30%, in addition to maximum oxygen consumption greater than 10 ml/kg/minMust have signed and dated an ICF before performance of any study-specific procedures or tests—subjects must be fully informed about their illness and the investigational nature of the study protocol

### Exclusion criteria

Patients requiring ICU care with mechanical ventilationPatients needing reintervention during postoperative carePatients requiring a thoracotomyTumor considered potentially resectable by incomplete surgical resection with microscopic residual disease (R1) or gross residual disease (R2)Evidence of extra-thoracic diseaseMajor thoracic surgical procedure before enrollmentAny other significant comorbid condition that, in opinion of the investigator, would impair study participation or cooperation

### Screening

Subjects are screened prior to the surgery. The following activities and/or assessments will be performed during screening:
Obtain written ICF from subject or subject’s legal representativeCollect subject’s medical historyRecord concomitant medicationsPerform physical examinationRecord vital signs, height and weightCollect blood sample for hematology, coagulation tests, blood chemistry, renal and liver function tests and measurement of electrolytes (obtain within 30 days prior to the surgery)Record 12-lead electrocardiogram (ECG)Record spirometry, hemogasanalysis and bronchoscopyPerform baseline CT scan, PET–CT scan and chest X-rayPerform anesthesiologic evaluation

### Device description

The Drentech™ Palm EVO device is a portable vacuum unit connected to a compatible collection system.

The collection system is a standard disposable drainage unit that can be connected to a chest drain, with a water-seal valve.

The unit is capable of generating suction that can be independently adjusted by a central vacuum and/or energy sources. The unit can be powered and/or the batteries recharged using the power supply provided.

The mobile unit is equipped with a display to show the following information:
Indication of the “instantaneous” air leakage corresponding to the last minute of operationMean air leakage value of the patient in the last hour of measurementIndication of the hours of device operation, calculated starting from the moment of activationHistory of the air leakages and minimum and maximum intrapleural pressures relating to the last 99 h of operation, available in numerical and graphic formMeasurement and storage of the minimum and maximum intrapleural pressure values of the patient relating to the last minute of operationReal-time measurement of the minimum and maximum intrapleural pressure values for each respiratory act of the patient

The unit can transfer data to a USB storage device in order to view and/or store them on a PC. The USB storage device can be connected to the dedicated port on the unit using the adapter provided, and the data can be viewed with standard spreadsheet programs or the RedaxPlot software provided.

### Randomization

A person not involved with either enrollment, assessments or training of participants will generate the allocation sequence. Individual randomization, stratified for centers and with blocking to reduce variability, will be performed with a 1:1 allocation to the intervention and control groups. The assignment to one of the two devices will be performed using closed envelopes containing notes reading either “T” for traditional water seal system or “D” for digital system. The randomization will be done in the surgical theater at the end of thoracoscopic lobectomy by one of the surgeons by opening the envelope assigned to the patient. Due to the nature of the intervention, neither participants nor investigators will be masked during the intervention.

### Intervention

The day of the surgery, after induction of anesthesia, a double-lumen endotracheal tube is used for selective ventilation of the lungs. During the procedure, patients are monitored by ECG, arterial line, pulse oximeter and urine output. Patients are placed in a lateral decubitus and undergo a VATS lobectomy associated with lymphadenectomy. During surgery, the patient receives fluid and, eventually, blood replacement, maintaining adequate blood pressure and urine volume. After VATS lobectomy, the presence of air leaks is tested by a water submersion test under standard airway pressure of 25 cm H_2_O and the air leaks are measured by a volumetric system. In the case of significant air leaks (i.e. more than 100 ml/min), application of sutures is allowed, whereas no buttressing material, sealants or pleural tents are permitted. At the end of the procedure, a single apical 28-Ch chest tube is placed.

Patients are then randomized 1:1 to receive two different types of chest drainage management: digital, connected to the Drentech™ Palm Evo system; or traditional, connected to the water-seal drain system already in use in each center. After surgery, patients are transferred to the ward.

Patients with the digital chest drainage system are managed by setting the pump to − 20 cmH_2_O from the moment the patient is extubated until the morning of the first postoperative day (POD) and then turning off the suction (0 cmH_2_O). Patients with traditional devices are connected to wall suction (− 20 cmH_2_O) until POD 1, and then they are disconnected from suction.

The following activities and/or assessments will be performed after surgery:
▪ Daily assessment of the cardio-pulmonary parameters (blood pressure, cardiac frequency, oxygen saturation) all through the hospitalization▪ Complete blood count, liver and renal functional tests the first day after surgery and then depending on the clinical condition of the patient or medical judgment▪ Chest X-ray immediately after the return to the ward and afterward depending on clinical condition of the patient or medical judgment; after drains are removed, another chest X-ray is performed before discharge

Postoperative treatments include respiratory rehabilitation and mobilization, and antithrombotic and antibiotic prophylaxis. Pain will be controlled by means of analgesic drugs according to each center’s analgesic protocol based on its routine practice (intravenous, epidural, intercostal block or mixed regimens).

The chest tube is removed when chest X-rays show a complete lung expansion and there is no detectable air leak on traditional devices. For digital devices, absence of air leaks is defined as a recorded airflow lower than 20 ml/min, with suction set at 0 cmH_2_O, for at least 8 h and without significant spikes of air leak on the graph. The daily fluid drainage threshold for drain removal is based on each center’s routine practice (generally 300 ml). During morning and evening rounds, the presence of an air leak and the pleural effusion volume are checked for both types of drain system. In particular, the Drentech™ Palm Evo is equipped both with the standard traditional “water-seal” system and with the digital electronic device: for the evaluation of correspondence between subjective clinical observation of air leaks and objective digital results, the presence of air leaks will be checked on each visit round by two clinicians via observation of bubbles in the chamber with the digital screen switched off in order to be blinded regarding the digital features. Then, the electronic screen is switched on and the data are recorded. For the purpose of clinical management, in this group of patients, the clinician responsible for the ward will consider only the features of the digital device.

In the case of a “pleural space” effect suspected on the basis of features of the digital system, a provocative clamping maneuver will be performed and a control chest X-ray at 24 h will be done for confirmation to decide on chest drain removal. Air leak duration is calculated, as usual, from the day of operation until the day an air leak is no longer detectable. Duration of air leaks for more than 7 days are considered prolonged air leaks and are managed according to each center’s routine (e.g. discharge with a portable chest drainage system or reoperation). Moreover, in these cases, the air leak duration will be measured and data will be collected until the 8th POD and no discharge from the hospital will be considered before that day.

### Follow-up

Postoperative follow-up will consist of a scheduled visit with chest X-ray about 30 days after discharge.

### Study termination and drop out

The patient has the right to terminate the research and evaluation at any time point, without sacrificing further medical treatment. There is no replacement of patients who withdraw from the study or who interrupt prematurely. The reason for discontinuation of the study will be given on the data collection form.

### Statistical analysis

Periodical checking of the input data will be performed in order to verify the completeness and consistency of the database.

Checks on the consistency and plausibility of the reported data will be carried out prior to data analysis.

The study is powered based on its primary endpoints: the duration of chest tube placement and the length of stay. The sample size was calculated to detect a difference in duration of chest tube placement and/or hospital stay after thoracoscopic lobectomy of at least 1 day and based on previously published data (standard deviation = 3) [5]. A sample size of 382 patients (191 patients per group) was determined based on 90% statistical power, with a significance level of 0.05, and allowing for dropouts.

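### The per-endpoint significance level and the claim supported by the two primary endpoints are worded inconsistently; one stated rule, preferably Holm, would settle both

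*Protocol article*

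**What the plan says.** Three places in the protocol article bear on how the two primary endpoints are to be judged.

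- **Primary outcomes** gives the objective: "To determine whether the use of a digital chest system compared with a traditional system reduces the duration of chest drainage and LOS". The Discussion repeats this aim.
- **Methods/design** (sample-size paragraph after Fig. 2) assumes a two-sided t test with "effect size = 0.33 for both primary endpoints", "power (1 – β) = 0.8" and "α = 0.025 accounting for a Bonferroni adjustment", that is 0.05/2.
- **Statistical analysis** states: "The study is powered based on its primary endpoints: the duration of chest tube placement and the length of stay". It then sizes the trial "to detect a difference in duration of chest tube placement and/or hospital stay after thoracoscopic lobectomy of at least 1 day", with an SD of 3, 90% power, a significance level of 0.05 and an allowance for dropouts of unstated size. The total is 382 patients, 191 per group.

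Methods/design also plans an interim analysis at 200 patients on the primary endpoint, in the singular. No section states which results make the trial positive.

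**The concern.** A Bonferroni split is needed when either endpoint alone may carry the claim. A rule that requires both endpoints needs no split. An unsplit 0.05 on each endpoint, with success on either, does not hold the family-wise error at 5%. The article contains a phrase that could be cited for each of these.

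Two things are at stake. The first is error control, if the 0.05 in Statistical analysis is applied to each endpoint and either result is enough. The second is the strength of the claim. The objective speaks of drain duration and LOS together, but the quoted power is for one endpoint at a time, and winning both is less likely than winning one. The trial is unmasked, so a rule settled late would be hard to defend.

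**Working it through.** **Inputs.** From Statistical analysis: difference 1 day, SD 3 (d = 1/3), 191 per arm, alpha 0.05, power 90%. From Methods/design: d = 0.33, alpha 0.025, power 80%, two-sided t test. The correlation between the endpoints is not in the article. I assume 0.5 and show 0 to 0.9.

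**1. The plan's own figure.** With d = 1/3, two-sided alpha 0.05 and 90% power, the t test needs 191 per arm, or 382. This matches exactly and leaves nothing for dropouts. With d = 0.33, alpha 0.025 and 80% power it needs 176 per arm, or 352, which reaches 382 only with about 8% dropout (1 − 352/382 = 7.9%). The stated total therefore rests exactly on the unsplit alpha in one section, and on the split alpha plus an unstated dropout rate in the other. Both calculations treat a single endpoint, so both power figures are per endpoint.

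**2. Power per endpoint at 191 per arm.** The expected test statistic is d·√(n/2) = (1/3)·√95.5 = 3.2575. In the normal approximation:

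- alpha 0.05: Φ(3.2575 − 1.9600) = 90.3% (t test 90.1%)
- alpha 0.025: Φ(3.2575 − 2.2414) = 84.5% (t test 84.3%)

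The 90% holds only without the split. At alpha 0.025, 90% power would need 450 (d = 1/3) to 460 (d = 0.33) patients in total.

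**3. Family-wise error when neither endpoint differs.** At correlation 0, each at 0.05 gives 1 − 0.95² = 9.75%, and each at 0.025 gives 1 − 0.975² = 4.94%. For the other correlations I used the bivariate normal distribution of the two test statistics.

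| Either endpoint wins | corr. 0 | 0.5 | 0.9 |
|---|---|---|---|
| each at 0.05 | 9.8% | 9.1% | 7.0% |
| each at 0.025 | 4.9% | 4.7% | 3.6% |

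**4. Power when both endpoints improve by 1 day.** At correlation 0:

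- Both under Bonferroni: 0.8452² = 71.4%.
- Both under Holm: both below 0.05 and at least one below 0.025, so 2 × 0.8452 × 0.9028 − 0.8452² = 81.2%.
- At least one, under either procedure: 1 − (1 − 0.8452)² = 97.6%.

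| 191 evaluable per arm, d = 1/3 | corr. 0 | 0.5 | 0.9 |
|---|---|---|---|
| at least one, Bonferroni or Holm | 97.6% | 94.0% | 88.8% |
| both, Bonferroni | 71.4% | 75.1% | 80.3% |
| both, Holm | 81.2% | 83.1% | 85.8% |
| one given endpoint, Bonferroni | 84.5% | 84.5% | 84.5% |
| one given endpoint, Holm | 89.4% | 88.5% | 87.3% |

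If only 176 per arm are evaluable and d = 0.33, the Bonferroni power for both is 69% at correlation 0.5 (65% to 75%).

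**The case against.** Much of the case on the other side stands. An objective that lists two endpoints joined by *and* is ordinary prose and need not mean that both must win. *And/or* is compatible with Bonferroni, and the only explicit multiplicity statement is the 0.05/2 split. The most natural combined reading is therefore either endpoint, each at 0.025. On that reading the 9% error disappears.

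A reader might infer more: that the article states three rival win rules, so the same data could give opposite trial conclusions. For example, p = 0.01 with p = 0.20 passes an either-endpoint Bonferroni rule and fails a both-at-0.05 rule, and p = 0.04 on each does the reverse. The article does not support this. It states no win rule, and a both-at-0.05 rule appears nowhere in it, so such reversals compare the documented split with a constructed alternative.

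A reader might also infer that Bonferroni is a mistake here. It is valid. Holm's case does not rest on the endpoints being correlated, and its gain shrinks as the correlation rises.

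The final decision rule may lie in an analysis plan that is not shown, so its absence is not the point. The point is that two sections give different alphas for the same 382 patients, and that the objective and the sizing statement word the claim differently. A separate plan would have to override one of them.

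**Conclusion.** The concern holds as an inconsistency in the stated significance level and in the claim, not as a set of contradictory win rules. If the unsplit 0.05 were applied to each endpoint with success on either, the family-wise error would be about 9% instead of 5%. If the split is kept, the stated 80% describes one endpoint. Power for the joint claim in the objective is then about 75%, and below 80% over nearly all of the correlation range.

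These figures assume normal test statistics, the same 1-day effect and SD of 3 on both endpoints, 191 evaluable per arm, no interim look and an assumed correlation. The per-endpoint figures and the correlation-0 results need no assumption about dependence beyond independence itself. Moving to Holm adds about 8 points for both endpoints at correlation 0.5 (about 10 at 0 and 6 at 0.9) and nothing to the chance of at least one win.

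**What to change.** Use one rule, worded the same way, in Primary outcomes, Methods/design and Statistical analysis. For example:

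*Drain duration and LOS are tested two-sided by the Holm procedure at family-wise alpha 0.05, or at what remains after any alpha spent at the interim analysis. The smaller p-value is compared with alpha/2 and, if it is significant, the larger with alpha. The trial is positive if at least one endpoint is significant. A reduction in drain duration and LOS is claimed only if both are.*

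Remove the unsplit per-endpoint 0.05, and the 90% power that goes with it, from Statistical analysis. State that the quoted power is per endpoint at 0.025, and give the dropout rate that leads to 382. If power for the joint claim is quoted, state the assumed correlation and the evaluable number.

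The cost is an amendment of wording, with no extra patients or data. Because the trial is unmasked and already recruiting, the change should be made and dated before any comparative results are seen, including those of the interim analysis. Holm rejects everything that Bonferroni rejects and keeps the same family-wise error. Its small downside is that matching simultaneous confidence intervals are less simple. If the team prefers Bonferroni, the rest of the fix still applies.

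### The sample of 382 is justified twice with incompatible alpha, power and dropout claims; 90% power holds only at unadjusted alpha 0.05 with no losses, and is about 84% at the Bonferroni alpha

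*Protocol article*

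**What the plan says.** The protocol article gives two sample size justifications, both current text.

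- **Methods/design** (text after Fig. 2): a two-sided t test for a difference in means, with "effect size = 0.33 for both primary endpoints, power (1 – β) = 0.8 and α = 0.025 accounting for a Bonferroni adjustment". No dropout allowance is mentioned. The total is 382.
- **Statistical analysis**: the trial is sized "to detect a difference in duration of chest tube placement and/or hospital stay after thoracoscopic lobectomy of at least 1 day", with a standard deviation of 3 taken from published data. The total of 382 (191 per group) was "determined based on 90% statistical power, with a significance level of 0.05, and allowing for dropouts". No dropout rate is given.

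The section on study termination and drop out adds: "There is no replacement of patients who withdraw from the study or who interrupt prematurely". The Randomization section places randomization at the end of the lobectomy, after consent and screening.

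**The concern.** The two statements agree on the effect (1 day / SD 3 = 0.33) and on the total, but not on alpha (0.025 or 0.05), power (80% or 90%) or dropout (not mentioned, or allowed for). One number cannot have been determined by both sets of inputs.

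Two things are at stake. First, readers and oversight bodies will rely on the 90%, and it may not be a property of this design. Second, the level at which an endpoint counts as positive is left unclear. A p-value of 0.03 on length of stay alone would pass at 0.05 and fail at 0.025. The Statistical analysis section treats an effect on either endpoint as a target and names 0.05 with no adjustment. If each endpoint were tested at 0.05, the trial-wise error would exceed 5%. The Trial status section also says recruitment runs until power is sufficient, which has no fixed meaning while two power targets stand.

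**Working it through.** **Inputs from the article.** Difference 1 day and SD 3 (Statistical analysis), so d = 1/3; d is also given as 0.33 (Methods/design). Two-sided t test (Methods/design). Allocation 1:1 (Randomization). 191 per group. Alpha 0.05 with 90% power, or alpha 0.025 with 80% power.

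**Formula.** The normal approximation per group is n = 2(z₁₋α/₂ + z₁₋β)² / d². With d = 1/3 this is 18(z₁₋α/₂ + z₁₋β)². The exact t-test figure comes from the noncentral t distribution and is about one patient per group larger.

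**Step 1: reproduce 382.** Alpha 0.05, power 90%: 18 × (1.960 + 1.282)² = 189.1. The noncentral t gives 190.1, so 191 per group and 382 in total. This is the stated number exactly, with a dropout allowance of zero.

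**Step 2: the other inputs.**

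| Alpha (two-sided) | Power | Normal approx., d = 1/3 | t test, d = 1/3 | Total | t test, d = 0.33 | Total |
|---|---|---|---|---|---|---|
| 0.05 | 90% | 189.1 | 190.1 → 191 | 382 | 193.9 → 194 | 388 |
| 0.025 | 80% | 171.1 | 172.4 → 173 | 346 | 175.8 → 176 | 352 |
| 0.025 | 90% | 223.4 | 224.7 → 225 | 450 | 229.2 → 230 | 460 |

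The Methods/design inputs reach 382 only with an unstated loss: 1 − 173/191 = 9.4% at d = 1/3, or 1 − 176/191 = 7.9% at d = 0.33.

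**Step 3: power of 191 per group.** The noncentrality is d√(n/2) = (1/3)√95.5 = 3.257.

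- Alpha 0.05: Φ(3.257 − 1.960) = 90.3%; the t test gives 90.1%.
- Alpha 0.025: Φ(3.257 − 2.241) = 84.5%; the t test gives 84.3% (83.5% at d = 0.33).

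**Step 4: effect of loss** (rates assumed, since the article gives none; t test, d = 1/3).

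| Loss | n per group | Power at 0.05 | Power at 0.025 |
|---|---|---|---|
| 0% | 191 | 90.1% | 84.3% |
| 5% | 181 | 88.6% | 82.2% |
| 10% | 172 | 86.9% | 79.9% |

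Holding 90% power at 0.05 with 10% loss would take 382 / 0.9 = 424.4, or about 425 patients.

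**Step 5: could a one-sided reading rescue the second statement?** One-sided 0.05 with 90% power gives 310 (d = 1/3) or 316 (d = 0.33). Reaching 382 would then imply 17% to 19% dropout, and it contradicts the stated two-sided test. It does not.

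**Step 6: error if both endpoints are tested at 0.05.** From the bivariate normal distribution under no effect, the chance of at least one false positive is 9.1%, 8.3% and 7.0% at correlations of 0.5, 0.7 and 0.9. The article gives no correlation, so these are assumptions.

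**The case against.** The strongest reply is that the trial is adequate as it stands. At 0.025 with 80% power it needs 346 to 352 evaluable patients, and 382 covers that with about 8% to 9% loss. This is correct. The finding is not that more patients are needed.

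A second reply is that 0.05 in the Statistical analysis section may mean the overall level that Methods/design then halves, and that neither passage is a decision rule for the final analysis. That is a fair reading of the words, and it means the family-wise figures describe a procedure the article does not spell out. The arithmetic does not support it as a description of the calculation, though: 90% power with 191 per group arises only if 0.05 is used unadjusted for one comparison. At the halved level, 90% is wrong by about six percentage points.

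Third, taking the effect size literally as 0.33 gives 176 rather than 173 per group. This is true and small; 173 is right for the 1 day and SD 3 that the article also states.

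Fourth, 191 per group already implies a count of allocated patients, so the gap between enrolled and randomized is a minor ambiguity. This also stands.

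Fifth, Holm in place of Bonferroni is an improvement and not a correction, since Bonferroni is valid. The contradiction must be resolved whether or not Holm is adopted.

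Finally, nothing in the article shows which calculation was operative, since 382 matches the second exactly. The case for keeping the first is that it alone fits two primary endpoints, multiplicity control and a dropout allowance.

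**Conclusion.** The concern holds. The two justifications are incompatible, and the second fails on its own inputs because 382 leaves no room for the dropout it claims to allow. The 90% requires both an unadjusted alpha of 0.05 and no losses. At the Bonferroni level the power is about 84% per endpoint with no loss and about 80% with 10% loss. The trial still meets an 80% target at 0.025, so the defect is an overstated power and an unresolved significance level, not too few patients.

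These figures rest on the article's 1 day and SD 3, a two-sided t test and equal groups. They take no account of the interim analysis planned at 200 patients. The loss rates and the correlations between endpoints are assumptions.

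**What to change.** Keep 382 and replace both statements with a single one along these lines:

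- There are two primary endpoints, with a family-wise two-sided alpha of 0.05.
- For 1 day and SD 3, 173 evaluable patients per group give 80% power per endpoint at 0.025.
- Randomizing 382 allows for about 9% loss; power is 84% per endpoint if nobody is lost.
- The 382 are counted as randomized, not as consented.

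Remove the 90% and the unadjusted 0.05 from the Statistical analysis section, and state the effect size once. If 0.33 is kept literally, the figures become 176 per group and about 8% loss.

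Test the endpoints by Holm's procedure: the smaller p-value at 0.025 and, if that is significant, the other at 0.05. It controls the same family-wise error and is never less powerful than Bonferroni. With 191 per group and a true effect of 1/3 on both endpoints, the chance of success on both rises from 75% to 83%, 77% to 84% or 80% to 86% at assumed correlations of 0.5, 0.7 or 0.9.

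The cost is wording only, with no extra patients. The stated power becomes less favourable, at 80% to 84% instead of 90%.
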